## Abstract

Treatment-Resistant Depression (TRD) poses a substantial health and economic challenge, persisting as a major concern despite decades of extensive research into novel treatment modalities. The considerable heterogeneity in TRD’s clinical manifestations and neurobiological bases has complicated efforts toward effective interventions. Recognizing the need for precise biomarkers to guide treatment choices in TRD, herein we introduce the SelecTool Project. This initiative focuses on developing (WorkPlane 1/WP1) and conducting preliminary validation (WorkPlane 2/WP2) of a computational tool (SelecTool) that integrates clinical data, neurophysiological (EEG) and peripheral (blood sample) biomarkers through a machine-learning framework designed to optimize TRD treatment protocols. The SelecTool project aims to enhance clinical decision-making by enabling the selection of personalized interventions. It leverages multi-modal data analysis to navigate treatment choices towards two validated therapeutic options for TRD: esketamine nasal spray (ESK-NS) and accelerated repetitive Transcranial Magnetic Stimulation (arTMS). In WP1, 100 subjects with TRD will be randomized to receive either ESK-NS or arTMS, with comprehensive evaluations encompassing neurophysiological (EEG), clinical (psychometric scales), and peripheral (blood samples) assessments both at baseline (T0) and one month post-treatment initiation (T1). WP2 will utilize the data collected in WP1 to train the SelecTool algorithm, followed by its application in a second, out-of-sample cohort of 20 TRD subjects, assigning treatments based on the tool’s recommendations. Ultimately, this research seeks to revolutionize the treatment of TRD by employing advanced machine learning strategies and thorough data analysis, aimed at unraveling the complex neurobiological landscape of depression. This effort is expected to provide pivotal insights that will promote the development of more effective and individually tailored treatment strategies, thus addressing a significant void in current TRD management and potentially reducing its profound societal and economic burdens.

## Background

1

It is imperative to improve our therapeutic strategies and provide optimal treatment options for depression. Major Depressive Disorder (MDD) is a substantial contributor to global disability, affecting more than 300 million people (1). Multiple lines of evidence suggest that MDD may stem from various pathophysiological changes (2), including disruptions in glutamatergic function (3). A significant challenge arises as approximately 30-50% of MDD patients exhibit inadequate responses to initial treatment approaches (4). Consequently, these individuals endure distressing symptoms for extended periods, with a significant portion developing treatment-resistant depression (TRD). TRD is operationally defined as the lack of a substantial therapeutic response after two antidepressant trials that are deemed adequate in both duration (specifically, a minimum of 4-6 weeks) and dosage (5). Studies have shown that individuals with TRD have reduced glutamate levels in prefrontal regions (6).

Recently, two rapid-acting interventions gained approval to address TRD: glutamatergic pharmacotherapies, such as esketamine nasal spray (ESK-NS), and non-invasive brain stimulation, specifically repetitive transcranial magnetic stimulation (arTMS), with accelerated protocols being able to exert similar antidepressant effectiveness to standard protocols with a reduced timeframe (7, 8). Both treatments require a significant time investment and are administered in specialized settings, but there is currently insufficient data guiding the choice between them. rTMS can locally modify cortical excitability in specific brain regions, inducing changes in brain circuits typically underactive in MDD (9). In contrast, ESK-NS acts on glutamatergic ionotropic N-methyl-D-aspartate (NMDA) receptors, transiently increasing glutamate release (10). The challenge of identifying personalized interventions for TRD and MDD remains a significant concern, with the absence of tools able to guide treatment selection as a prominent issue. Coupling effective treatments with suitable patients reduces costs, chronicity, and avoidable suffering (4).

Addressing the “treatment-selection” problem requires a deeper understanding of biomarkers in depression: objectively measurable characteristics reflecting underlying biological processes that contribute to heterogeneity of the MDD subtype and predict the therapeutic response (11–13). Resting-state electroencephalography (EEG), a neuroimaging technique known for its high temporal resolution, appears to be a promising approach for response prediction in depressive illness (14). It is a valuable tool to explore neural biomarkers associated with TRD, offering information on neural activity alterations and functional connectivity related to depression. Evidence suggests that EEG-derived biomarkers, such as alpha band asymmetry, altered EEG resting-state B microstate, or EEG functional connectivity patterns, could accurately help predict treatment outcomes (15–17).

Peripheral blood-based biomarkers, such as markers of systemic inflammation (including interleukines: IL-6, IL-8, IL-2p70) and hormone levels (thyroid-stimulating hormone, cortisol, norepinephrine) can also aid in subtyping MDD and predicting treatment response (18).

These biomarkers are easy to measure and have significant potential for practical implementation in routine clinical practice. Additionally, computational phenotyping, which generates research-grade profiles based on clinical presentation and computer-executable algorithms, contributes to a comprehensive understanding of personalized treatment approaches (19).

Machine learning (ML), a subset of artificial intelligence, encompasses diverse algorithms capable of building predictive models based on specific datasets (20). These algorithmic approaches aim to reveal fundamental principles underlying observations without explicit instructions, extracting structured knowledge from extensive datasets (21). A recent review demonstrates that ML technologies and data analytics can be applied at various stages of the patient journey, including detection and diagnosis, prognosis, treatment selection and optimization, outcome monitoring and tracking, and relapse prevention. Furthermore, data-driven ML approaches can identifying subtypes of symptoms and cognitive deficits, enabling model-based phenotyping (22). In this regard, significant progress has been made in the field of oncology. Specifically, it has become possible to robustly predict treatment responders and non-responders by using network-based biomarker expression levels in patients with melanoma, metastatic gastric cancer, and bladder cancer treated with immune checkpoint inhibitors targeting the programmed cell death 1/programmed cell death ligand 1 axis (23). On the other hand, integrating ML methods with extensive electronic health record databases has the potential to facilitate personalized psychiatry (22).

In this area, to fill the gap between the largely unmet needs of TRD and the enormous potential that has been opened by available innovations (e.g., neuroscience techniques, artificial intelligence methods, and advanced therapeutics), computerized tools can be developed, integrating clinical, neurophysiological, and peripheral data to guide treatment selection. These machine-learning methods could overcome the difficulty of treating TRD and its devastating consequences.

This study aims to develop and preliminarily validate a computational system that integrates clinical, electroencephalographical, and peripheral marker data, thus creating a tool to inform the treatment of Treatment-Resistant Depression (TRD) called “SelecTool”. This tool is designed to support clinical decision-making by helping select personalized, tailored interventions. Using a machine-learning analysis of multi-channel data, the SelecTool will guide treatment selection towards ESK-NS or arTMS. This manuscript delineates the study protocol of the SelecTool project, a translational, multicentric investigation encompassing two distinct phases that aim to develop a machine-learning based tool to help guide clinicians in managing TRD.

## Methods/design

2

### Study design and settings

2.1

The project comprises two phases (**Figure 1**). The first (WP1; see **Figure 1**) involves the development of SelecTool for treatment orientation towards ESK-NS and arTMS by creating a machine-learning system. This phase includes:

**Figure 1 f1:**
[figure not shown]
Flow chart of the study protocol describing the two different phases.

• Prospective evaluation of clinical, electrophysiological, and peripheral biomarkers to predict the antidepressant response to ESK-NS and arTMS (n = 100).

• Integration of the above data with those previously collected from subjects with TRD treated with ESK-NS (n = 50) and arTMS (n = 50).

• Training a computerized system to develop a machine-learning-based tool that guides the treatment selection.

The subsequent stage (WP2; see **Figure 1**) focuses on the pilot validation of the ESK-NS and arTMS prescription using SelecTool, including the proof-of-concept estimation of SelecTool’s accuracy in an independent cohort (n = 20; out-of-sample validation). In this step, the identified biomarkers guiding treatment will be integrated into the SelecTool model as input data. Using the SelecTool’s output, individuals will undergo nonrandomized assignment to ESK-NS or arTMS interventions. Therefore, the accuracy in determining an increase in the number of responders to treatment will be estimated and compared with the response rates observed in random assignment.

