### Sample size and eligibility criteria

2.2

One-hundred and twenty subjects (WP1: 100 subjects; WP2: 20 subjects) who are diagnosed with major depressive episode (both during the course of MDD or bipolar disorder) according to the Diagnostic and Statistical Manual of Mental Disorders, 5th edition (24), will be recruited by three Research Units: the ‘G. d’Annunzio’ University of Chieti, the University of Milano, and the Tor Vergata University of Rome.

The inclusion criteria will be the following: age between 18 and 65; current major depressive episode within at least the past month; TRD, defined as the absence of clinical response despite two or more treatments with antidepressants at adequate doses for 4-6 weeks (5); current stable psychopharmacological therapy for at least 1 month.

The exclusion criteria will be the following: presence of severe organic or neurological comorbidities, any substance use disorder (except nicotine dependence) in the past 6 months, intellectual disability or decline (Mini-Mental State Examination, MMSE < 26); uncontrolled systemic hypertension (specific for safety of ESK-NS treatment); presence of a positive history of seizures in the patient’s history or a first-degree relative (specific for arTMS safety); pregnant and postpartum women.

To refine the processing precision of the tool, we will consolidate the dataset from participants enrolled in the study with clinical data gathered retrospectively. These supplemental data will be obtained from a dedicated TRD dataset, which includes information from subjects who met identical inclusion and exclusion criteria and underwent prior treatment in our centers with ESK-NS (n = 50) and arTMS (n = 50).

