### Treatment administration

2.8

During the first phase (WP1), subjects will be randomly assigned in a 1:1 ratio to receive arTMS or ESK-NS. A stratified randomization approach with a four-block size will be implemented to minimize inadvertent bias. Stratification factors will include sex (male, female), age (expected cutoff 50 years old), depression severity (mild/moderate depression, MADRS ≤ 34; severe depression, > 34), and treatment site (Chieti, Milan, and Rome). The randomization process will be carried out by an investigator external to the study.

In the pilot validation phase (WP2), the extracted treatment-guiding biomarkers will be incorporated into the SelecTool model as input data. Subsequently, subjects will be allocated to esketamine or arTMS interventions based on the output of the SelecTool.

All subjects will undergo a comprehensive preliminary visit to assess potential contraindications to treatments. Qualified medical personnel, specifically trained to handle potential side effects and emergencies related to treatments, will administer ESK-NS and arTMS treatments.

Subjects in the ESK-NS group will be administered the drug according to the EMA guidelines (49). It will be supplied in a double-use nasal spray device containing 200 μl of vehicle solution (two sprays), each delivering 28 mg (14 mg ESK-NS base per 100 μl of spray). This dose will be administered twice a week for the first week, followed by 84 mg (three devices) administered twice a week for three weeks, resulting in a total of 1 month of treatment. Before initial administration, patients will be instructed to blow their nose (only before the first device is administered) and then assisted to recline their head 45° (semi-reclined position) during administration to enhance retention of the medication within the nasal cavity. Each ESK-NS session will be conducted by qualified personnel who closely monitor vital parameters (blood pressure, heart rate) before and at 45 and 90 minutes after treatment, following international safety guidelines (50).

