### Statistical analysis

2.9

Drawing from the existing literature on the efficacy of arTMS and ESK-NS for Treatment-Resistant Depression (TRD), we anticipate a response rate of approximately 50% for each treatment (52, 57). The sample size was determined using the G*Power 3.1 software, taking into account specific parameters: a substantial effect size of predictors (expected Cohen effect size F = 0.4), power 1-beta = 0.80, one-way, four groups (2x2; treatment: ESK-NS, arTMS; responders and non-responders), and a significance level corrected for multiple comparisons (alpha = 0.001). These calculations resulted in a total sample size of n = 144. Considering a possible imbalance in the allocation of responders (10%) and to mitigate possible dropouts (10%), we increased the total sample size to n = 200.

We will develop a machine-learning model to predict the primary treatment outcome and use it for treatment guidance. This model will leverage both neurophysiological data and clinical scores. We also aim to interpret the model and extract the features that influence it. Given the heterogeneous nature of the collected data, an appropriate solution is to opt for ensemble methods, particularly random forest techniques, which have shown suitability for such tasks (19, p. 202) and are relevant for *post hoc* analysis of results. To provide comprehensive insights, our exploration will not be restricted to random forest techniques; we will also investigate other approaches such as neural networks or support vector classifiers. Dealing with missing values in clinical and psychometric tests is a critical concern, and we will address this using advanced techniques such as multivariate imputation (58, 59). The model parameters and performance will be assessed using nested and shuffle cross-validation, which is recognized as optimal to minimize bias in model error estimations (60). The results’ significance will be evaluated using permutation tests, which are acknowledged as the gold standard for statistical assessments of machine-learning algorithms (61).

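### Half of the data behind the ESK-NS versus arTMS selection rule is retrospective and apparently non-randomised, with identical eligibility as the only stated safeguard

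*Protocol article*

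**What the plan says.** All references are to the protocol article.

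- **Randomised part.** Section 2.8: "During the first phase (WP1), subjects will be randomly assigned in a 1:1 ratio to receive arTMS or ESK-NS", stratified by sex, age, severity and site.
- **Added patients.** Section 2.1, in the list of WP1 steps under Figure 1: "Integration of the above data with those previously collected from subjects with TRD treated with ESK-NS (n = 50"), and likewise 50 treated with arTMS. The next step in that list is training the tool.
- **Nature of the added data.** Section 2.2: "we will consolidate the dataset from participants enrolled in the study with clinical data gathered retrospectively". They come from "subjects who met identical inclusion and exclusion criteria and underwent prior treatment in our centers with ESK-NS (n = 50) and arTMS (n = 50").
- **Numbers.** Section 2.2 recruits "One-hundred and twenty subjects (WP1: 100 subjects; WP2: 20 subjects"). Section 2.9 derives 144 from an ANOVA calculation and raises it to 200.
- **Use and assessment.** Section 2.9 says that the model predicts response and then guides treatment. It is assessed by nested and shuffle cross-validation and by permutation tests. No data set is named for either.
- **External check.** WP2 assigns 20 new patients by the tool's output and compares their response with that under random assignment (section 2.1).

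**The concern.** The tool's product is a choice between two treatments. What it must learn is how the ESK-NS versus arTMS difference in response varies between patients. Randomisation in WP1 protects that contrast. Adding as many patients again, treated earlier in routine care, removes the protection from half of the data.

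Identical eligibility closes some routes of channelling, because patients with uncontrolled hypertension or a seizure history are excluded from both sources. It does not remove the reasons why one eligible patient was given ESK-NS and another arTMS, nor differences between sites and periods.

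If the test folds are drawn from the consolidated set, the same confounding sits in training and test data, so internal validation cannot separate it from true differential response. WP2 patients would then be assigned by a rule that may partly reflect past prescribing.

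**Working it through.** **1. Where n = 200 comes from.** Inputs from section 2.9: f = 0.4, alpha = 0.001, power 0.80, four groups. Method: one-way fixed-effects ANOVA, noncentral F with lambda = N × f², df1 = 3, df2 = N − 4.

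- N = 144: lambda = 144 × 0.16 = 23.04, power 0.805. The smallest N is 143, or 144 with equal groups. The plan's 144 is reproduced.
- Inflation: 144 / 0.9 / 0.9 = 177.8, or 144 / 0.8 = 180. The stated 200 is more generous.
- Patients available: 100 (WP1) + 50 + 50 (retrospective) = 200. Prospective recruitment, including WP2, is 120. So 200 is met only by counting the retrospective patients, who are 100/200 = 50% of the set.

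**2. Power on the same inputs by sample.**

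| N | lambda | power |
|---|---|---|
| 200 (pooled) | 32.0 | 0.96 |
| 144 (plan) | 23.04 | 0.805 |
| 100 (randomised) | 16.0 | 0.52 |
| 90 (randomised, 10% dropout) | 14.4 | 0.44 |

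**3. Possible bias, by simple arithmetic.** The article gives nothing on past allocation, so these are assumptions. Take equal treatments and about 50% response. Let a prognostic factor shift response by 20 to 30 points and differ in prevalence between the retrospective arms by 20 to 60 points.

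- Spurious difference in the retrospective half = shift × imbalance: 0.20 × 0.20 = 4 points, up to 0.30 × 0.60 = 18 points.
- In the pooled data, half of that: 2 to 9 points. In the randomised half the expected value is 0.
- Standard error of the difference: √(2 × 0.25/50) = 10 points with 50 per arm, and √(2 × 0.25/100) = 7.1 points with 100 per arm.

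Pooling gains precision, but the bias can be of the same order as the standard error.

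**4. Possible bias, by simulation.** Each data set has 100 randomised and 100 retrospective patients and no true treatment effect. Response depends on one unmeasured factor. Past allocation depends on a measured marker and that factor, either additively or through their product. The fitted logistic model has marker, treatment and their interaction. The same log-OR per SD is used for response and for allocation. Runs used 1,500 to 4,000 data sets per scenario.

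| Past allocation | log-OR | Term tested | Randomised 100 | Pooled 200 |
|---|---|---|---|---|
| additive | 1 | treatment | about 5% | 20–21% |
| additive | 0.5 | treatment | about 5% | about 7% |
| additive | 1 | interaction | about 5% | about 5% |
| product | 1 | interaction | 4–5% | 18–19% |
| product | 0.5 | interaction | about 5% | 6–7% |

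The bias in the first row is +0.33 log-odds, about 0.33 × 0.25 = 8 points near 50% response.

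**5. Can WP2 detect it?** With 20 patients and 50% response, the standard error of the response rate is √(0.25/20) = 11 points, before any uncertainty in the comparator. A distortion of 2 to 9 points is not visible at that size.

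**The case against.** The case against has real weight.

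- **Non-randomised status is inferred.** The article does not say outright how the earlier patients were allocated. Retrospective data on prior treatment at the centres make non-randomised allocation the natural reading.
- **The data set for cross-validation is not named.** Section 2.9 is silent, and the Abstract speaks only of training on WP1 data. Fold composition is the kind of detail that an article may leave to a fuller document. What the article does fix is consolidation for building the tool (sections 2.1 and 2.2), a sample size that needs it, and one safeguard.
- **Presence and size of bias cannot be derived.** At log-ORs of 0.5 the false-positive rates are near nominal. Under additive allocation the interaction, which personalised selection relies on, is not distorted even at log-OR 1. The false interaction needs allocation by a product of marker and factor, which is a special mechanism.
- **Protection is weakened, not lost.** Half of the data stay randomised and stratified, and WP2's benchmark is response under random assignment. Confounding would reach WP2 through the rule, not through that comparator.

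Two stronger readings are tempting and should not be drawn. A reader might infer that EEG and blood values will be imputed for the retrospective cohort, since section 2.2 calls those records clinical data and section 2.9 says "we will address this using advanced techniques such as multivariate imputation". The sentence in section 2.9 limits imputation to clinical and psychometric tests, so no such plan is stated. A reader might also infer that cross-validated performance would look good because of the confounding. In the same kind of simulation at log-OR 1, pooled cross-validated accuracy was only 51 to 52%, against 49.9% with all 200 randomised. The documents give no basis for that claim.

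**Conclusion.** The concern stands in a limited form. As written, the plan trains a treatment-choice rule on a contrast that is half non-randomised, relies on those patients to reach n = 200, and offers only shared eligibility to make the sources comparable. If internal validation uses the consolidated set, it would not expose the resulting confounding, and WP2 is too small to do so.

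The illustrated size runs from almost none to material: about 7% to 21% false positives for the treatment term, and about 6% to 19% for the interaction under product-type allocation only. This rests on three assumptions: that the earlier patients were not randomised, that an unmeasured prognostic factor influenced past choice, and that its strength lies in the range shown. The power figures rest only on the plan's own inputs.

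**What to change.** 1. Compute every outer-fold performance figure and every permutation test on the randomised WP1 patients only.
2. Let retrospective records enter training folds only, with cohort and site indicators. An indicator absorbs a shift in response between sources but not confounded choice within the retrospective cohort, so the next step is also needed.
3. Report the model trained with and without the retrospective records.
4. State in section 2.9 that n = 200 includes 100 retrospective patients, and that the randomised 100 alone give power of about 0.52 on the plan's inputs (0.44 with 90 evaluable). Align the Abstract, which does not mention the retrospective records.

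**Cost.** Steps 1 to 3 change analysis wording and code. Intervals for reported performance widen, because the test set is 100 patients rather than 200. Step 4 puts a less favourable power figure on record. Going further and learning the contrast from randomised patients alone would be a trade-off: it removes this source of bias but leaves the sample 44 short of the plan's own 144, so it would need a revised sample-size justification.

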The field of psychiatry has also seen considerable advancements through pioneering research efforts. A recent multicenter study applied multimodal machine learning methods, integrating clinical, neurocognitive, structural magnetic resonance imaging, and polygenic risk scores to predict the onset of psychosis in individuals at high clinical risk or with recent-onset depression (65). Furthermore, a recent narrative review investigated the application of machine learning in diagnosing and forecasting schizophrenia, concluding that various machine learning-based models can potentially help healthcare professionals in diagnosing the condition and predicting its clinical presentations and complications (66).

Concerning TRD, a very recent machine learning study has highlighted that characteristics such as profound anhedonia, anxious distress, mixed symptoms, and bipolarity in patients treated with ESK-NS represent factors that predict a positive response and remission. In contrast, the use of benzodiazepines and the severity of depression were associated with delayed responses (67). The levels of accuracy achieved with data exclusively symptom-based do not allow for incorporation into clinical practice and justify the attempt of the SelecTool Project to refine selection methods by integrating other biomarkers.

Given the substantial global health impact of TRD, which doubles the risk of hospitalization and increases the risk of suicide sevenfold compared to treatment-responsive depressed patients (68) our primary objective is to identify treatment approaches that optimize patients’ prospects for recovery. On the one hand, arTMS is a proven intervention for TRD, strongly supported by existing literature, demonstrating response rates of 40–50% and remission rates of 25–30%. (52, 69). On the other hand, in patients treated with ESK-NS, the percentage of remitters has been observed to be less than half (70).

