As a result, despite the established antidepressant efficacy of ESK-NS and arTMS, achieving clinical response rates of approximately 50-60% even in real-world studies (8, 71–75), there remains a notable gap in our understanding of their response biomarkers. This proposal is also set to significantly expand our understanding of the complex and heterogeneous nature of the pathophysiology and treatment of MDD. Viewing MDD through the lens of brain connectivity disorders highlights its varied neurobiological foundations, likely related to disparate brain network functionalities (76). Such neurobiological diversity leads to distinct MDD subtypes, each with its unique treatment response profile, particularly to neuromodulation and glutamatergic interventions.

By deepening our understanding of the biomarkers associated with various depression subtypes, including clinical, EEG, and peripheral indicators, we aim to pioneer a patient-centered approach to treatment selection. Given the substantial social, occupational, and physical repercussions associated with TRD, not to mention the increased healthcare costs that make TRD a significant economic burden on healthcare systems (68, p. 201; 77, 78), this research has the potential for considerable social and economic benefits.

In conclusion, this research proposal not only aims to change the approach to treating TRD by leveraging cutting-edge machine learning techniques and comprehensive data analysis, but also aims to shed light on the intricate landscape of the neurobiological underpinnings of depression. Through this endeavor, we anticipate contributing valuable insights that could influence and offer potential advantages for clinical practice, facilitating the development of more effective and personalized treatment regimens. This approach addresses a critical gap in the current management of TRD and potentially alleviating its significant societal and economic impacts.

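### WP2 compares SelecTool only with random assignment; if the arms differ on average, a gain over the pooled rate need not reflect matching of patient to treatment

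*Protocol article*

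**What the plan says.** The Abstract gives the purpose of SelecTool: to "enhance clinical decision-making by enabling the selection of personalized interventions". Section 2.8 (Treatment administration) states that in WP1 "subjects will be randomly assigned in a 1:1 ratio to receive arTMS or ESK-NS"; with 100 subjects this is about 50 per arm. In WP2, section 2.1 (Study design and settings, text after Figure 1) says that "individuals will undergo nonrandomized assignment to ESK-NS or arTMS interventions" according to the tool's output, in a separate cohort of 20 described as a pilot validation and proof of concept. The same paragraph sets the benchmark: the tool's success in raising the number of responders "will be estimated and compared with the response rates observed in random assignment".

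On response rates, section 2.9 (Statistical analysis) states that "we anticipate a response rate of approximately 50% for each treatment". The Discussion gives 40–50% for arTMS and later describes both treatments as "achieving clinical response rates of approximately 50-60% even in real-world studies". Section 2.9 also plans nested and shuffle cross-validation and permutation tests for a model that predicts the primary outcome. Nowhere does the article compare the tool's assignments with giving every patient ESK-NS, or every patient arTMS.

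**The concern.** The benchmark and the aim answer different questions. Beating random assignment shows that the tool does better than a coin toss between the two treatments. Personalisation requires more: that the particular patients sent to each treatment gain from being sent there. If one treatment works better on average, a rule that uses no biomarker and simply favours that treatment also beats the pooled random rate. A higher WP2 response rate could then be credited to the EEG, blood and clinical inputs when it reflects only the average difference between treatments. That would be a weak basis for collecting 64-channel EEG and blood markers to choose treatment. A larger WP2 would not remove the problem, because it lies in the reference and not in the precision.

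**Working it through.** The article gives no figure for the WP2 comparison, so there is nothing of its own to reproduce on this point. Its sample size of 144 concerns predictor effects across four groups, not this comparison.

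**Inputs from the article.** WP1: 100 patients randomised 1:1, about 50 per arm. WP2: 20 patients assigned by the tool. Planning response: about 50% per arm. Discussion ranges: 40–50% for arTMS, 50–60% for both treatments.

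**Assumptions.** WP1 and WP2 patients are comparable. The random-assignment rate is the pooled WP1 rate; the 100 retrospective patients are not described as randomised and cannot supply it. The arm gaps and the tests below are illustrative, because the article states neither.

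**1. Decompose the gain.** Let pB and pW be the mean response on the better and worse treatment, Δ = pB − pW, s the share sent to the better treatment, and C the covariance between assignment to the better treatment and the individual treatment effect. Only C is patient matching.

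- Response under the tool: pW + sΔ + C
- Pooled 1:1 rate: pW + Δ/2
- Gain over random assignment: (s − 1/2)Δ + C
- Gain over WP1 arm rates weighted by the tool's split (pW + sΔ): C
- Gain over the better treatment for everyone (pW + Δ): C − (1 − s)Δ

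**2. Set C = 0 (no matching).** The expected gain over random assignment is:

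| Arm rates | Δ | s = 0.75 | s = 1 |
|---|---|---|---|
| 50% / 50% | 0 | 0 | 0 |
| 50% / 55% | 5 points | 1.25 points | 2.5 points |
| 40% / 50%, 45% / 55% or 50% / 60% | 10 points | 2.5 points | 5 points |
| 40% / 60% | 20 points | 5 points | 10 points |

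Example: for 50% / 60% and s = 1, (1 − 0.5) × 10 = 5 points (60% against a pooled 55%). Against the split-weighted reference, every cell is zero.

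**3. What an observed WP2 result would look like with C = 0** (exact binomial enumeration, 20 patients against 50 + 50):

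| Arm rates | s | WP2 rate numerically higher | Two-sided 5% Fisher test, in favour of the tool | One-sided 5% pooled z-test |
|---|---|---|---|---|
| 50% / 50% | any | 48% | 2.0% | 4.9% |
| 10-point gap | 0.75 | 56–57% | 3.1–3.3% | 7.3–7.7% |
| 10-point gap | 1 | 64–65% | 4.8–5.2% | 10.6–11.1% |
| 40% / 60% | 0.75 | 65% | 4.5% | 10.2% |
| 40% / 60% | 1 | 78.5% | 10.3% | 19.9% |

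Under the one-sided test, simulation against the split-weighted reference gave rejection rates of 4.7–5.5% in all scenarios.

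**4. Which s is plausible.** In simulation with 40% / 60% arms and 200 training patients, a ridge-logistic tool without interactions sent everyone to the better arm in over 99% of runs. With pure-noise interactions it sent 68–83% there (62–75% with 100 training patients). Section 2.9 favours random forests, which can fit interactions, so the 75% rows are probably nearer to the planned tool than the 100% rows.

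**5. Cost in precision.** At 50% response, the half-width of a 95% interval for the difference is 1.96 × √[0.25 × (1/20 + (s² + (1 − s)²)/50)]. This gives 24.0 points at s = 0.5 (equal to using the pooled 100), 24.5 at s = 0.75 and 25.9 at s = 1.

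**The case against.** Four points on the other side have force.

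- **The pooled reading is inferred.** The article speaks of response rates in the plural and does not mention pooling. Split-weighted WP1 arm rates would also be rates observed under random assignment, so the remedy can be seen as specifying the sentence. This stands, and it is why the stated comparison can be kept and sharpened.
- **No passage shows that the arms differ.** At the planning value of 50% each, the bias is zero. The Discussion gives an arTMS range and a joint range, but never sets 40% for one treatment against 60% for the other. The 20-point row is therefore a stress case. Equally, nothing in the article makes the interpretation safe if WP1 does show a difference.
- **WP2 is a 20-patient pilot.** False significance is modest: about 2–10% with a two-sided Fisher test across the scenarios. The larger one-sided figures depend on a test that the article does not state.
- **Random assignment is a reasonable first benchmark** when, as the Background says, data to guide the choice are lacking. It should stay, but it cannot carry the personalisation claim by itself.

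Cross-validation and permutation tests do not answer the point. They are described for a model that predicts outcome, not for the tool's assignments set against a fixed-treatment rule.

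A reader might infer that the trial is set to declare personalised selection with no personalisation at all, or that its false-positive rate is seriously inflated. The article supports neither: the first needs a real arm difference and a confirmatory reading of a pilot, and the second needs a lenient test and an extreme allocation.

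**Conclusion.** The concern holds in a limited form. The only WP2 reference named in the article cannot separate patient–treatment matching from an average difference between arms, if it is read as the pooled 1:1 rate. The spurious expected gain is (s − 1/2)Δ: 2.5 to 5 points for a 10-point gap with 75% to 100% of patients sent to the better arm, and zero if the arms are equal as planned. The consequence is mainly one of interpretation. With a 10-point gap and no matching, the WP2 rate would look numerically better in 56–65% of trials, against 48% with equal arms. The result rests on comparable WP1 and WP2 patients, 50 per WP1 arm, and arm gaps that the article does not assert. WP1 will show whether a gap exists, so the reference is best fixed before those data are seen.

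**What to change.** In section 2.1, keep the comparison with random assignment and add the following:

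1. Report how many WP2 patients SelecTool assigned to ESK-NS and to arTMS.
2. Compare the WP2 response rate with the WP1 randomised arm-specific rates weighted by that split, with a 95% confidence interval. Name this as the check for patient–treatment matching.
3. Separately, report the gain over giving everyone the better single treatment: descriptively for WP2, and by cross-validation for WP1 with the better arm chosen inside the training folds. Name this as the check of whether the tool is worth using over one treatment for all. It is a stricter question than item 2, since a tool can match patients to some extent and still fall short of the better arm.
4. State that a gain over random assignment alone will not be described as evidence of personalisation.

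This changes analysis and reporting text only; no new patients or measurements are needed. The costs are that the reported gain may be smaller and that the WP2 interval widens slightly, by up to about 2 points in half-width (24.0 to 25.9) if all patients go to one arm.
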